### **27.a Reporting and assumptions/statistical methods to handle missing data**

As missing primary outcome values (DEP-ADO scores at 48 months post-intervention) might depend on observed data and/or missing data, and due to the large amount of missing data for the binary primary outcome at 48 months post-intervention (see CONSORT flow diagram, Appendix 2), primary analysis will be performed with imputation for missing data using Multiple Imputation (MI). Missing data will be imputed under Missing At Random (MAR) assumption, and odds ratios estimates for each imputed data set will be obtained. The imputation will be repeated 20 times and Rubin's rule will be used to combine estimates and standard errors.

This represents a change to the original analysis protocol, which did not acknowledge that the potential bias in only considering data that from participants who were available for follow-up. Outcomes are expected to be affected by risk status and substance use outcomes, therefore intent-to-treat analysis will include all participants. Furthermore, as missing data is also at random and highly dependent on participant simply being present on the day of testing at school, there are also cases of missing data at only one timepoint of the 5 assessments. Omitting participants on the basis of one missing timepoint (i.e., listwise) would lead to very large attrition and lost data that would otherwise be useful in the evaluation of the outcome (either through estimate final outcome, or by providing outcomes at other timepoints).

## **28. Other analysis**

Exploratory analyses not identified in the SAP will be clearly identified in the reporting as well as any deviation in the analyses from this original SAP.

## **29. Harms**

There is a risk to implementing interventions with youth, in that certain prevention programs have shown negative effects, including consistent negative effects in non-cognitive-behavioural counselling and social work interventions. However, the proposed personality-targeted interventions incorporate therapeutic techniques associated with beneficial outcomes and have been shown to have substantial positive effects in three separate populations across Canada and the United Kingdom for individuals participating in interventions, as well as indirect population-level benefits across the school grade.

There are possible risks in implementation of selective interventions by educational professionals in a school context, both for adolescent participants and facilitators. The targeted nature of the programme necessitates a careful introduction of the study and interventions to participants in order to avoid participants being labelled or stigmatised. All self-report data will be kept confidential and parents and teachers consent to not having access to their child's self-report information. Selection criteria are kept confidential and are only revealed to the staff members who are trained to deliver the programme and who undergo careful training on the importance of confidentiality around this programme. This programme works with educational professionals and school counsellors who are professionally trained to deal with issues of confidentiality, student distress and at risk cases. A clinical psychologist will be available to provide research staff and schools with additional clinical support should issues of risk be revealed. These concerns have been addressed and evaluated throughout the delivery the Adventure Trial, a teacher-delivered personality-targeted intervention trial, as well as during intervention delivery by psychologists. The proposed protocol is designed to minimise any risk to those involved.

As such, we decided it was not necessary to perform interim data analyses.

## **30. Statistical Software**

SAS Statistical Software, Version 9.4

**31.b Reference to Data Management Plan**

Study was conducted under the Good Clinical Data Management Practices (GCDMP) and the Good Clinical Practices (GCP).

**31.c Reference to Trial master file and statistical master file****31.d Reference to other Standardized operating procedures or documents**

## APPENDIX

### Appendix 1: Timing of outcome assessments

| Primary Outcome                                                                                         |                    |
|----------------------------------------------------------------------------------------------------------------|--------------------|
| Measure                                                                                                 | Time Frame  |
| DEP-ADO: Self-reported alcohol and drug problems ( $\geq 18$ )                                                 | At follow-up 4     |
| Secondary Intermediate Outcomes                                                                         |                    |
| Measure                                                                                                 | Time Frame  |
| Global cognitive function:                                                                                     |                    |
| Adaptation of the Cultures Figure Task (CFT)                                                      | At each time point |
| Adaptation of the 'Dot Location' test, a subtest of the Child Memory Scales (CMS)                 | At each time point |
| Executive function:                                                                                            |                    |
| Adaptation of the Go/No-Go Passive Avoidance Learning Paradigm (PALP)                          | At each time point |
| 'Find the phone' is a task based on the Self-Order Pointing Task                                  | At each time point |
| Other secondary outcomes                                                                                |                    |
| Measure                                                                                                 | Time Frame  |
| DEP-ADO  age of drinking and substance use onset, binge drinking items                            | At each time point |
| SDQ  : Conduct problems, peer problems, emotional problems and hyperactivity/inattentive symptoms | At each time point |
| Depression and anxiety symptom severity (BSI)                                                                  | At each time point |
| Unauthorized absences                                                                                          | At each time point |
| Attendance, absence and drop-out                                                                               | At each time point |

**Appendix 2: CONSORT diagram for the final study sample (Co-venture flow diagram)**

Figure 2. The percentages in this diagram represent the proportion of participants followed each year on the initial group size at baseline.

[figure not shown]

\*Missed participation: The participant was absent or refused to participate that specific year.

\*\*Lost to follow-up: The participant has left the school either for academic, conduct, moving reasons.

**Appendix 3: Additional information on Outcome measures.**

Table 3: Summary of outcomes, measures and time of assessment.

| Outcomes         | Variable                                                  | Measure (items)                                                                                           | Grade at time of assessment |
|------------------|-----------------------------------------------------------|-----------------------------------------------------------------------------------------------------------|-----------------------------|
| Primary   | Substance abuse/dependence                                | DEP-ADO total score $\geq 18$ (DEPAPO_ECHELLE_TOTAL)                                                      | 8, 9, 10, 11                |
|                  | Global cognitive function                                 | Global cognitive function:                                                                                |                             |
|                  | • Non-verbal functioning and abstract reasoning           | • Adaptation of the CFT (IQ)                                                                              | 8, 9, 10, 11                |
|                  | • Verbal and visual memory (immediate and delayed recall) | • Adaptation of the CMS (DLR)                                                                             | 8, 9, 10, 11                |
|                  | Executive functioning                                     | Executive function:                                                                                       |                             |
| Secondary | • Cognitive control and response inhibition               | • Adaptation of the PALP (INH)                                                                            | 8, 9, 10, 11                |
|                  | • Spatial working memory                                  | • 'Find the phone' task (WM)                                                                              | 8, 9, 10, 11                |
|                  | Substance use onset and binge                             | • Substance use onset (DEPAPO_ALC_OC2, DEPAPO_DRUG_OC1)
• Binge items (DEPAPO_ALC_OC5, DEPAPO_ALC_OC8) | 8, 9, 10, 11                |
|                  | Mental health symptoms                                    | • Emotional problems scale (SDQ_echelle_emotion_prob)                                                     | 8, 9, 10, 11                |
|                  |                                                           | • Conduct problems scale (SDQ_echelle_conduct_prob)                                                       |                             |
|                  |                                                           | • Hyperactivity scale (SDQ_echelle_hyper_prob)                                                            |                             |
|                  |                                                           | • Peer problems scale (SDQ_echelle_peer_prob)                                                             |                             |
|                  |                                                           | • SDQ total score (SDQ_echelle_total_difficulties)                                                        |                             |
|                  | School attendance and drop-out                            | • Depression (BSI_echelle_TotalDepression)                                                                | 8, 9, 10, 11                |
|                  |                                                           | • Anxiety (BSI_echelle_TotalAnxiete)                                                                      |                             |
|                  | School attendance and drop-out                            | Unauthorized absences (DEM_06_Y1 )
Attendance, absence and drop-out (ATT)                              | 8, 9, 10, 11                |

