#### **2. Secondary intermediate outcomes** are neuropsychological functions, for which two hypotheses will be investigated regarding the possible effects of delaying early substance use:

- a. **Global Effects Hypothesis:** substance use and binge drinking will have global harmful effects on cognition and interventions that successfully prevent substance use onset will result in global

improvements in cognitive function in participants who received the intervention relative to those randomized to control condition.

- b. Critical Developmental Period Hypothesis: the toxic effects of alcohol and drug use are developmentally specific, so effects of interventions will be observed on cognitive processes that are maturing in adolescence, namely, executive functions and reward sensitivity, after controlling for general IQ and memory function following procedure described by [name], et al.[71].
3. **Secondary outcomes** will be measures of poor mental health and functional cognitive measures such as academic achievement and school drop-out.

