#### *2.8 What are the proposed primary and secondary outcome measures?*

The **primary outcomes** of this study are self-report alcohol and illicit drug use measures in high-risk youth, including onset of drinking, binge drinking and illicit drug use, within the first two years of the follow-up, and longer-term reductions in substance use disorders in later years, assessed according to a score greater than 20 on the 'Detection of alcohol and drug problems in adolescents' questionnaire (DEP-ADO [97]). This tool has demonstrated good construct validity, internal consistency, test-retest and intermodal execution reliability in Quebec youth. Self-report measures have been found to have excellent discriminant [98] and predictive [99] validity with regards to adolescent substance-related behaviours and problems [25-27, 69] This questionnaire captures quantity, frequency of drinking, binge drinking and illicit drug use, as well as symptoms of substance abuse and dependence, reliably identifying youth with alcohol use disorders [100]. Youth who screen positive on this task will be contacted outside of the school setting to participate in a confidential phone or face-to-face interview, in which DEP-ADO will be administered by a clinician to confirm substance use disorder diagnosis.

**Intermediate secondary outcomes** are cognitive functioning. Global cognitive functioning, executive function and reward sensitivity will be assessed using neuropsychological measures relating to each of the hypotheses outlined in section 1.2. All cognitive tasks will be administered annually, during a 50-minute class period using computerised neuropsychological batteries developed, validated and shown to predict future academic and work performance by PI [name] et al. [100] and physical aggression by PI [name] et al. [71].

1. Global Effects Hypothesis will be tested using a computerised progressive matrices task [101] and a general knowledge task based on that used in [71], as proxies for global cognitive functioning. A pattern recognition task, a spatial recall task, verbal recall task and a visual reproduction recall task will be used to measure immediate and delayed visual and verbal memory, following [name] et al. [100]. Similar cognitive scales have identified youth with alcohol use disorders [37].

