2. Critical Developmental Period Hypothesis will be tested using two developmentally sensitive neuropsychological measures administered using the computerised battery of dorsolateral prefrontal tasks developed by [name] et al [100]. One task, adapted from the Go/No-Go Passive Avoidance Learning Paradigm (PALP; [102]) will be used to assess cognitive control and response inhibition (see Appendix H). Commission errors on this task are commonly used as an index of response inhibition [103], and commission errors and reaction time to reward trials relative to punishment trials can be used as an index of reward sensitivity [52]. This task is

sensitive to individual differences in response inhibition under different reinforcement contingencies and with French and English-speaking adolescents and parallel forms exist for repeated administration [100, 103, 104]. The self-ordered pointing task [50] is a test of non-spatial executive working memory (Appendix H). This task is a sensitive measure of executive working memory in children [105], has been computerised and used to investigate working memory capacity in French and English-speaking adolescents at risk for substance misuse [71, 106].

**Other secondary outcomes:** Academic performance will be recorded by requesting access to students' school grades and provincial exam scores. School attendance, retention and drop-out will be requested from schools, with parent and student consent, data that 95% of schools were willing to provide in the Adventure RCT [28, 29]. Self-report mental health symptoms will be assessed by the Strengths and Difficulties Questionnaire [107], used in French-computerised format by the PI in the IMAGEN multi-site study of 2000 European 14-year olds [104]. Population level effects on substance use and cognitive outcomes will be examined to be sure that any benefits of the intervention on HR youth are not offset by possible negative or null effects on the non-targeted low-risk youth.

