## 10. Sample size calculation for the primary outcome

Sample size calculations are conducted according to the sample needed for the primary long-term analyses, namely the onset of substance use disorders 4-years post-intervention in the sub-group of students identified at high-risk in grade 7. As the school (cluster) is the unit of randomisation, the sample size determination accounts for the clustering of students within schools. According to data from a local epidemiologic study and a previous personality-targeted intervention trial, the expected proportion of students with a substance use disorder in grade 11 in the control group is 10%. The minimum detectable reduction is set to 50% (i.e., 10% substance use disorders in grade 11 in the control group versus 5% in the intervention group). Assuming that this proportion per school is approximately normally distributed (i.e., 95% of the schools would fall within two standard deviations of the mean, 10%, 7 %), we obtain a between-cluster coefficient of variation,  $k$ , of 0.35. In addition, we expect 50 students per school (40-45% of the full sample) to be identified as high-risk (average cluster size of 50), following previous personality-targeted intervention studies. With these assumptions (using formula 7.7,), the number of schools (clusters) per arm needed to detect a 50% reduction in the proportion of drinkers (i.e., from 10% to 5%) with 80% power and a false positive error rate of 2.5% is 15, giving a total of 30 schools or approximately 1500 high-risk students. We plan to recruit two additional schools ( $30 + 2 = 32$  schools total) to account for potential attrition at the school-level.

For the secondary outcomes (other measures of substance use, mental health and cognition), we will use the observed effect sizes from the IMAGEN study on 2000 14 year-old European participants who completed neuropsychological assessments. Binge drinkers showed reduced IQ and a greater reward bias on the Passive Avoidance Learning Paradigm^45 relative to non-bingers where observed effect sizes ( $d$ ) for these mean differences ranged

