## **14. Visit map: Outcomes and main interest variables collection time points**

Outcomes and timing are presented in Visit Map Table 1 in details. Table 1 presents the outcomes and other variable that were collected at different time points. The length between follow-ups in each school is 12-month.

Table 1. Schedule of enrolment, interventions, and assessments of the study in schools.

|                                |                                                       | Pre-Intervention | Intervention period | Post-Intervention
Number of months after the initiation of the intervention |          |          |          |               |
|--------------------------------|-------------------------------------------------------|------------------|---------------------|--------------------------------------------------------------------------------|----------|----------|----------|---------------|
| Categories                     | Variables                                             | Baseline         |                     | 12-month                                                                       | 24-month | 36-month | 48-month | Variable type |
| Primary outcomes        | Substance use disorder                                | •                |                     | •                                                                              | •        | •        | •        | Continuous    |
| Secondary substance use | Non-verbal functioning and abstract reasoning         | •                |                     | •                                                                              | •        | •        | •        | Continuous    |
|                                | Verbal and visual memory                              | •                |                     | •                                                                              | •        | •        | •        | Continuous    |
|                                | Cognitive control and response inhibition             | •                |                     | •                                                                              | •        | •        | •        | Continuous    |
|                                | Spatial working memory                                | •                |                     | •                                                                              | •        | •        | •        | Continuous    |

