### **26.b Adjustments for primary and secondary outcomes**

To take into account the baseline prognostic factors at the cluster (school) level used for DA (c.f. Section Randomisation), all the results will be adjusted for language of the school, and the gender with three categories.

In case of imbalance for a variable at baseline, interaction and confounding effects will be tested according to its clinical significance.

Modification to protocol: Considering that immigration status has a very large protective effect on youth substance use (including in this sample), and that schools in Montreal vary significantly on this variable, we have modified the analysis plan to also include immigration status (immigrant, first generation, second generation) as a covariate.

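### The SAP gives the full Critical Developmental Period Hypothesis no pre-specified test: reward sensitivity and the IQ/memory control are both missing, and no reason is given

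*Combined protocol and SAP*

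**What the plan says.** **Protocol.** Section 1.2 sets a Global Effects Hypothesis beside a Critical Developmental Period Hypothesis. The second predicts effects on maturing processes, "namely, executive functions and reward sensitivity, after controlling for general IQ and memory function". Section 2.8 repeats the three domains as intermediate secondary outcomes: "Global cognitive functioning, executive function and reward sensitivity will be assessed using neuropsychological measures". It also gives the derivation from the PALP: "commission errors and reaction time to reward trials relative to punishment trials can be used as an index of reward sensitivity".

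**SAP outcomes.** Section 7 restates neither hypothesis. The visit map (section 14, Table 1) has a row for "Cognitive control and response inhibition" and none for reward. Appendix 1 lists the PALP once, under executive function. Appendix 3, Table 3 has a single PALP entry, "Adaptation of the PALP (INH", beside a working-memory task (WM). The section on analysis methods for secondary outcomes (26.c) ties those analyses to Appendix 3.

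**SAP adjustment.** Under 26.b, "all the results will be adjusted for language of the school, and the gender with three categories". Immigration status is added there as a modification. IQ and memory appear in the SAP only as outcomes.

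**SAP effect size.** Section 10 still draws on earlier findings for both measures: "Binge drinkers showed reduced IQ and a greater reward bias on the Passive Avoidance Learning Paradigm", with d from 0.23 to 0.25.

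**The concern.** The two hypotheses are rivals. The first expects general cognition to move; the second expects movement specific to executive function and reward processing, beyond general cognition. Telling them apart is the purpose of the cognitive battery. If the SAP is followed as written, it produces separate models for CFT, CMS, inhibition and working memory. It reports nothing on reward sensitivity and states no rule for deciding whether an executive effect is specific or part of a general shift.

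The silence matters too. The SAP records small departures, such as one extra CMS item and self-reported truancy, as well as an added covariate and a changed missing-data method. A protocol-named outcome and a stated control are gone with no entry. Any later reward or IQ/memory-controlled analysis would have to be reported as exploratory or as a deviation, because the SAP (sections 4 and 28) says so of analyses it does not identify.

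**Working it through.** The point is one of scope, so the main check sets the places side by side.

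| Element of the hypothesis | Protocol | SAP outcome lists or adjustment set |
|---|---|---|
| Response inhibition | 2.8, PALP commission errors | Present (INH) |
| Executive working memory | 2.8, self-ordered pointing | Present (WM) |
| Reward sensitivity | 1.2 and 2.8, PALP reward versus punishment trials | Absent from Table 1, Appendix 1 and Table 3 |
| Control for general IQ | 1.2 | Absent from 26.b; CFT is an outcome only |
| Control for memory | 1.2 | Absent from 26.b; CMS is an outcome only |

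One of two constructs and both controls are missing. The places where a change would be recorded (18.c, 18.d, 26.b, 26.c, 27.a and the closing deviation list) mention none of them.

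**Were the tasks given?** Appendix 1 lists the PALP, CFT and CMS at each time point, and Table 1 marks their constructs at baseline and at 12, 24, 36 and 48 months.

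**Would baseline IQ and memory adjustment separate the hypotheses?** Take the SAP's own powered effect of 0.20 SD.
- If everything moves by 0.20, baseline CFT and CMS are on average equal between randomised arms. The adjusted executive effect is still 0.20. The contrast of executive minus general effects is 0.20 − 0.20 = 0.
- If only executive scores move by 0.20, the adjusted executive effect is again 0.20. The contrast is 0.20 − 0 = 0.20.

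The adjusted effect is the same in both cases; only the contrast differs.

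**The plan's cognitive power figure.** Section 10 states at least 90% power with 15 schools per arm, 50 students per school, difference 3.0, SD 15.0, intra-cluster correlation 0.40 and a 2.5% error rate.
- Design effect = 1 + (50 − 1) × 0.40 = 20.6.
- Effective n per arm = 15 × 50 / 20.6 = 36.4.
- Standard error = 15 × √(2/36.4) = 3.52, and 3.0/3.52 = 0.85.
- Power = Φ(0.85 − 1.96) = 13.4% at one-sided 2.5%, or 8.3% at two-sided 2.5%.

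The figure is not reproduced; 90% would need a correlation of about 0.009 (one-sided 2.5%). This is a separate problem, but it limits what any cognitive comparison here can show.

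**Quality-control loss.** SAP section 20 rejects 17.6% of PALP records: 50 × (1 − 0.176) = 41.2 per school. At an assumed correlation of 0.01 and two-sided 5%, power falls from 88.7% to 84.4%. At 0.40 it stays at 13.4%.

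**The case against.** A reader might infer that the hypothesis can no longer be tested. The documents do not support that. The tasks were given at every wave, the executive half is still analysed, and the four retained outcomes give partial evidence: effects confined to INH and WM would favour the second hypothesis, and effects on all four the first. What is missing is a pre-specified test of the whole.

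A reader might also infer that the SAP's effect size rests on the omitted measure. Reward bias is one of two sources. IQ is the other and is retained, and the powered value of 0.20 is described as cognitive functioning in general.

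Nor do the documents show that the removal was deliberate. The SAP confines itself to main secondary variables, its section 25.a refers to a variable directory that is not in the file, and INH is not defined. A reward variable could be listed there. This weakens the point but does not remove it, because the analyses are tied to Appendix 3.

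Two further objections stand in part. Protocol 1.2 takes the IQ/memory control from a cited procedure, so whether baseline or concurrent values were meant is unknown. And secondary outcomes are described in SAP section 16 as supportive and exploratory, which limits the severity.

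**Conclusion.** The point holds as a gap in pre-specification. Reward sensitivity, a protocol-named intermediate secondary outcome, is in none of the SAP's three outcome lists. The stated control for IQ and memory is not in the adjustment set, and neither removal is explained. The full Critical Developmental Period Hypothesis therefore has no planned test, although the tasks it needs were administered. The primary analysis is unaffected.

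Two assumptions remain. The first is that the adapted PALP kept separately scored reward and punishment trials, as protocol 2.8 implies but the SAP does not state. The second is that the unseen variable directory does not already define a reward score for analysis.

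**What to change.** 1. Confirm that the adapted PALP scores reward and punishment trials separately. If it does, add the protocol 2.8 index (commission errors and reaction time, reward relative to punishment trials) to Table 1, Appendix 1 and Table 3 as a secondary outcome in the same model. If it does not, record the removal and the reason.
2. In 26.b, add baseline CFT and CMS as covariates for the executive and reward outcomes, for precision and chance imbalance. Baseline values avoid conditioning on variables measured after randomisation.
3. State how specificity will be judged: contrast the standardised intervention effect on executive and reward scores with that on CFT and CMS, with a confidence interval.
4. The closing deviation list shows that analysis has already begun. Date the change and label it as a return to a protocol outcome.

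The cost is SAP wording and one further score from a task already given. The downsides are one more exploratory test without multiplicity adjustment, on a task with 17.6% of records rejected.
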